### Inclusion and exclusion criteria

Inclusion criteria- Children (aged 5–15 years old) presenting with their parents, who are referred to the paediatric dentistry department in Dubai Dental Hospital (DDH) [the only secondary specialist dental hospital in Dubai, United Arab Emirates (UAE)], for dental treatment under N_2_O within a 6 months’ period will be invited to participate in the study.- Healthy children indicated for dental treatment under N_2_O with American Society of Anesthesiologists (ASA) classification of I or II.^13^- No learning disabilities impeding N_2_O sedation acceptance.UAE and non-UAE nationals’ parents and children will be eligible to participate in the study.- The children should have no previous experience of N_2_O inhalation sedation.Exclusion criteria- Medically compromised children and/or individuals with special healthcare needs.- Patients diagnosed with a psychiatric disorder.- Children who lack communication due to languages barriers.- Children whose parents refuse to participate in the study.- Patients with contraindications for the use of N_2_O, such as patients who have upper respiratory tract infections (common cold), mouth breathers due to nasal adenoids.- Patients with obvious skin conditions such as eczema or psoriasis that may impede the use of the E4^®^ wrist bands and impair their conductivity.

### Study flow and layout

A layout of the clinical study is presented in the flowchart seen in Fig. 1. After the initial examination by the clinical investigator, eligibility verification, participant’s assent and parents’/guardian’s signing the informed consent, the study participants will be randomly assigned to either the control or study group (33 patients per group). The study group will include families (children and parents) who are in need of N_2_O sedation at DDH (Dubai, UAE), who would attend a visit for prevention where N_2_O sedation will be introduced and experienced while the control group will be the families who would attend for a prevention visit and discussion of the sedation procedure only without any actual introduction to N_2_O.

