**Fig. 1 Fig1:**
[figure not shown]
Flowchart of the study design.

A 1:1 allocation-based block randomisation method will be employed. The method of allocation concealment will be attained by using matching, sealed, serially numbered, non-transparent envelopes that will contain group allocation. The envelopes will be opened in sequence by a non-investigator (dental assistant), only after the envelope has been conclusively dispensed to each partaker and will continue to be anonymous to the clinical team.

At the initial screening visit, the anxiety level will be recorded using MCDASf (Fig. 2) to determine the need for N_2_O sedation and subsequently invite the child and parents to participate in the study. Once enroled, an acclimatising visit will be carried out by a single paediatric dentist who will not be involved in the subsequent treatment of the patients. To be constant, an information script will be organised and rehearsed so that the same preoperative instructions about N_2_O sedation will be delivered to all the children and their parents. The patient’s physiological signs will be recorded using the E4^®^ wrist band (Fig. 3). For the study group only, 15 min of N_2_O sedation will be administered without any dental treatment procedures at the acclimatisation visit.

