### Calculation of the study’s sample size

The study is sized to have an 80% power to detect a statistically significant difference in children’s behaviour and anxiety level between the two groups. As there are no previous similar studies, the primary outcome measure is a change in anxiety (a reduction mainly). To our knowledge, no studies had investigated the effect of an acclimatising session of N_2_O on the child’s behaviour to base our sample size calculation on. Our biostatistician used Houpt et al. study in 1996 (effects of nitrous oxide on diazepam sedation of young children) to predict the sample size.^18^ The predicted sample size is 33 participants in each group and to compensate for dropouts a total of 70 participants will be recruited for both groups.

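### Allocation is placed before the explanation that both arms share, so the dentist giving it may know the arm; opening the envelope after the explanation would remove this

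*Protocol article*

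**What the plan says.** All references are to the protocol article.

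- **When children are assigned.** Study flow and layout puts assignment after these steps: "After the initial examination by the clinical investigator, eligibility verification, participant’s assent and parents’/guardian’s signing the informed consent". At that point "the study participants will be randomly assigned to either the control or study group", with 33 per group.
- **What each arm then attends.** The study group has a prevention visit at which N2O is introduced and experienced. For the other arm, "the control group will be the families who would attend for a prevention visit and discussion of the sedation procedure only".
- **Who runs the visit.** In the text after Fig. 1, once the child is enrolled, "an acclimatising visit will be carried out by a single paediatric dentist who will not be involved in the subsequent treatment of the patients".
- **What is common to both arms.** A script is rehearsed so that "the same preoperative instructions about N_2_O sedation will be delivered to all the children and their parents". The study group alone then has 15 minutes of N2O at this visit.
- **How the envelope is handled.** A dental assistant who is not an investigator opens the envelopes in sequence, "only after the envelope has been conclusively dispensed to each partaker". The same sentence says that allocation stays unknown to the clinical team.
- **Who is blinded.** Materials and methods names the dental surgeon and physiologist investigators. The text after Fig. 3 adds a second dentist, blinded to group, who scores the Frankl scale (FBRS) at the treatment visit.
- **Allowance for losses.** Under the sample size heading the requirement is 33 per group and, "to compensate for dropouts a total of 70 participants will be recruited for both groups".

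**The concern.** The trial asks what a trial experience of N2O adds to an explanation that is otherwise the same. That contrast is clean only if the explanation really is the same in both arms. A rehearsed script fixes the words, but not the tone, the time taken or the reassurance offered. A dentist who knows that one child is about to receive N2O and another is not could prepare them differently without intending to. A family that already knows its arm could also listen differently, or decide differently about attending.

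The blinded FBRS rater does not protect every outcome. The MCDASf is self-reported. The parents' questionnaire asks whether they have concerns about how the sedation works, which is close to the content of the script. Families are not listed among those blinded.

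The article itself gives reasons to think that the arm could matter to families. In the pilot, 8 of 15 children preferred to start without an acclimatising session. Strengths and limitations concedes that the additional N2O intervention and contact time may affect compliance.

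**Working it through.** **1. Order of events, as far as the text fixes it**

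| Step | Common to both arms? | Position relative to assignment |
|---|---|---|
| Examination, eligibility, assent, consent | Yes | Before |
| Prevention | Yes | After |
| Rehearsed sedation script | Yes | After |
| 15 min of N2O | Study group only | After |
| Opening of the envelope | – | Only after it is dispensed to the participant; not placed relative to the script |

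Two components common to both arms therefore follow assignment. Nothing described needs the arm to be known until N2O would start. The article does not set out the order of prevention, script and N2O within the visit. That the explanation comes before the N2O is the natural reading, but it is a reading.

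**2. Who can be unaware of the arm**

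The person who gives N2O to one arm and not the other knows the arm from that moment. The single dentist running the preparatory visit therefore cannot be among those kept unaware throughout. The two blinding statements do not clearly cover this dentist, who takes no part in later treatment. The claim that allocation stays unknown to the whole clinical team is thus too broad. It can hold for the treating dentist, the FBRS rater and the physiologist.

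**3. Does later opening gain power?**

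Inputs: 33 per group, 70 recruited and 80% power (sample size section); p < 0.05 (statistical analysis section), taken as two-sided. No effect size or SD is given, so 33 per group cannot be reproduced. It can only be back-solved:

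- Implied standardised difference: d = √(2/33) × (1.960 + 0.842) = 0.69.
- Spare children: 70 − 66 = 4, and 4/70 = 5.7%. The total of 70 agrees with a 5% loss, since 66/0.95 = 69.5, rounded up to 70.

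The article gives no figure for non-attendance between consent and the preparatory visit. Taking 5% to 10% as an assumption, 0.05 × 70 = 3.5 and 0.10 × 70 = 7 children. Approximate power is Φ(d√(n/2) − 1.960), with n per group and d = 0.69:

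| Assumed loss | Analysed of 70 | n per group | Power |
|---|---|---|---|
| 0% | 70 | 35 | 82.3% |
| 5% | 66.5 | 33.25 | 80.3% |
| 10% | 63 | 31.5 | 78.1% |

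Now move assignment to after the script. If 70 families consent and 10% do not attend, 63 remain to be assigned, the same number as before. To have 70 attend, 70/0.90 = 77.8, so 78 families must consent under either order. At 5% the figure is 70/0.95 = 73.7, so 74. Later assignment moves these losses to before randomisation, where they cannot depend on the arm. It does not recover the children.

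**The case against.** The strongest reply is that nothing here is an error. Randomising after consent is conventional. The article has a non-investigator open the envelopes, a rehearsed script, a single dentist kept apart from later treatment, and a blinded FBRS rater. A condensed article need not give the minute at which an envelope is opened, and Fig. 1 is not available. The text even permits the timing recommended here. All of that stands, and it limits the point to a better choice of order together with one clarification about blinding.

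A reader might infer three stronger things that the document does not support:

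- **That the dentist does know the arm while giving the script.** The opening time is not stated. Foreknowledge is allowed by the stated order but not shown.
- **That 3.5 to 7 randomised children will be lost before the arms differ.** The 5% to 10% rate is assumed. A separate interval between consent and the preparatory visit is not certain either: the abstract and the primary outcome section place treatment at the second visit, so screening and preparation could share one attendance, while the text after Fig. 1 speaks of an initial screening visit.
- **That the visit-2 FBRS assessment is unblinded.** The rater's blinding is unaffected, although a difference in how children were prepared could still show in their behaviour.

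The safeguards are nevertheless partial. Opening by an assistant protects the allocation before it is made, not conduct after it. A script limits variation in an explanation without excluding it. And no safeguard keeps the arm from the person who gives the N2O.

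**Conclusion.** The point holds as a design improvement, not as an error that undermines the trial. Assignment is placed ahead of two components that both arms share, and the dentist who delivers the script also gives the arm-specific N2O. This leaves room for performance bias in the explanation and for early loss that depends on the arm. A different order would close both. Separately, the statement that the clinical team stays unaware of allocation cannot be true of this dentist once N2O is given, and should be narrowed.

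The size of the possible bias cannot be derived from the document. The power illustration (80.3% at 5% loss, 78.1% at 10%) rests on an assumed loss rate and a back-solved d of 0.69. It describes losses under either order and is not a benefit of the change. The conclusion assumes that the script comes before the N2O within the visit. The argument about arm-related loss also needs an interval between assignment and that visit, which the article leaves open.

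**What to change.** In Study flow and layout, state that the dental assistant opens the next envelope at the preparatory visit, for every child, after prevention and the script are finished and just before N2O would start.

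In the same place, replace the general statement about the clinical team with a specific one: the dentist running the preparatory visit is unblinded from the moment of opening, while the treating dentist, the FBRS rater and the physiologist remain blinded.

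Also state how many children are to be randomised, since Study flow and layout gives 33 per group and the sample size section recruits 70. If assignment moves to this visit, recruitment should continue until that number has been assigned, because families who leave earlier still have to be replaced.

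The text cost is two or three sentences. The practical cost is that each preparatory slot, with its equipment and about 15 minutes of chair time, must be ready for either arm, including for children who turn out to be controls.

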### Role of the participants and the general public in the study

*What was the research question, the outcome and outcome measures of the study and how were they developed?* A pilot questionnaire to explore the usefulness of an N_2_O acclimatising appointment prior to actual treatment, from the participants’ point of view was carried out in a group of 15 child participants (range: 5–15 years). The outcome of this survey was indecisive with 8 out of 15 children expressing a predilection for commencing treatment without an acclimatising session to N_2_O. This resulted in the formulation of the primary outcome measure of our study on investigating the differences in the participants reported dental anxiety scale in children belonging to the study and control groups.

*What were the preferences and experiences of the participants and their influence in designing the study?* We asked the aforementioned children regarding their feeling in carrying out the completion of the MCDASf (anxiety survey). All the children in this survey mentioned that completing MCDASf was acceptable to them. In addition, we showed and placed the E4 watch on their wrists and asked if they would be happy to wear the watch throughout the treatment. Out of 15 children, 13 were happy with wearing the E4 watch; 2 children found it uncomfortable.

*Involvement of participants in the recruitment to and conduct of the study*. The potential participants will already be patients indicated for N_2_O sedation and are on the DDH sedation list.

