### The study’s statistical analysis

We will conduct deep statistical analysis after consideration of the data’s distribution normality, with the appropriate parametric or non-parametric statistical tests using the statistical software SPSS™ 24.0.0 (SPSS^©^ Inc., USA). The utilisation of standard descriptive statistics and quantitative data will be reported; if normally distributed, means and standard deviations shall be used; and if skewed, medians and interquartile ranges will be reported. The score of dental anxiety will be calculated for each participant and test for normality by using the Shapiro–Wilk test. Categorical data will be tested for independency by using Chi-square or Fisher's exact test when appropriate. The difference in the means between the two groups will be tested using either *t*-test or Mann–Whitney test depending on the normality of the data. The comparison of the means of more than two variables will be tested by using ANOVA or Kruskal–Wallis depending on the normality of the measurements. A *p*-value of <0.05 will be considered significant in all tests.

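### The protocol randomises 33 children per group in one section, but another needs 33 per group after dropout and recruits 70, so stopping at 66 leaves no cover for losses after randomisation

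*Protocol article*

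**What the plan says.** Two sections of the protocol article give a number per group.

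- *Study flow and layout*: after examination, eligibility check, assent and consent, children are "randomly assigned to either the control or study group (33 patients per group"). That is 2 × 33 = 66 randomised.
- *Calculation of the study's sample size*: "The predicted sample size is 33 participants in each group and to compensate for dropouts a total of 70 participants will be recruited for both" arms. Here 33 per group is what the calculation requires, and 70 is the intake that allows for dropout.

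The allocation ratio is fixed: "A 1:1 allocation-based block randomisation method will be employed". Seventy children at 1:1 means 35 per group.

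The power claim attached to the required size is "The study is sized to have an 80% power to detect a statistically significant difference in children’s behaviour and anxiety level between the two groups". No dropout rate, effect size or standard deviation is given.

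**The concern.** A required size and a number randomised differ by the allowance for losses. Here both are given as 33 per group, while the total to be recruited is 70. A team working from the study-flow section would stop at 66, and a team working from the sample-size section would go on to 70. The sealed, numbered envelopes have to be prepared for one total.

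The order of events makes this matter. Randomisation comes straight after consent. The first study visit follows, and treatment comes at the second visit. The behaviour rating, the post-treatment anxiety score and the acceptance questionnaires are all collected at or after that second visit. A child who misses it has already been randomised. With only 66 randomised, nothing replaces that child, and the stated 80% power no longer has 33 evaluable children per group behind it.

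**Working it through.** **Inputs**

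- Required size: 33 per group, 66 in total (sample-size section).
- Recruitment target: 70 (sample-size section).
- Number assigned: 33 per group (study-flow section).
- Ratio: 1:1 (text following Fig. 1).
- Power: 80% (sample-size section).
- Significance level: "A *p*-value of <0.05 will be considered significant in all tests" (statistical analysis section). Sidedness is not stated, so two-sided is assumed.

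**Step 1: can the 33 be reproduced?** No, because the effect size and standard deviation are not in the article. It can only be solved backwards for the effect that 33 per group detects with 80% power:

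d = (1.960 + 0.842) × √(2/33) = 0.69 by the normal approximation, or 0.70 by the t-test.

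**Step 2: can the 70 be reproduced from 66?** The allowance is 70 − 66 = 4 children, and 4/70 = 5.7% of those recruited. Using N/(1 − loss):

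- 5% loss: 66/0.95 = 69.5, rounded up to 70
- 5.7% loss: 66/(1 − 4/70) = 70
- 6% loss: 66/0.94 = 70.2, rounded up to 71

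So 70 fits a loss of about 5% to 5.7%, provided that 70 is the number entering randomisation.

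**Step 3: what remains under each reading?** Evaluable children per group = (number randomised) × (1 − loss)/2. Power is from the two-sided t-test at 0.05 with d = 0.70.

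| Randomised | Loss | Evaluable per group | Power |
|---|---|---|---|
| 70 | none | 35 | 82% |
| 70 | 5.7% | 70 × 0.943/2 = 33 | 80% |
| 66 | none | 33 | 80% |
| 66 | 5.7% | 66 × 0.943/2 = 31.1 | about 77% |

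The normal approximation for the last row, at 31 per group, agrees: 0.690 × √(31/2) − 1.960 = 0.755, which corresponds to a power of 77%.

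**Step 4: does the pilot supply a loss rate?** The section on participant involvement reports: "Out of 15 children, 13 were happy with wearing the E4 watch; 2 children found it uncomfortable". Discomfort was reported by 2/15 = 13.3%, with an exact 95% interval of 1.7% to 40.5%. The 5.7% allowance lies inside that interval. If the true rate were 5.7%, the chance of 2 or more in 15 would be 1 − 0.943^15 − 15 × 0.057 × 0.943^14 = 0.21 (using the unrounded 4/70). The pilot therefore does not conflict with the allowance, even if every uncomfortable child were counted as lost.

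**The case against.** The strongest reply is that the intention can be recovered. The sample-size section states the allowance and its purpose, so the figure in the study-flow section may simply repeat the evaluable target. Alternatively, the four extra children may cover losses between recruitment and randomisation. The first reading is plausible, but the sentence describes assignment, and a reader who follows it literally stops at 66. The second fits poorly, because randomisation comes directly after consent and leaves little room for losses before it. What stands is that this is an error of wording, with a modest effect on power.

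It is also fair to object that the power figures rest on a back-solved effect and a two-sided t-test, when the article states no sidedness and allows a Mann–Whitney test. They show the size of the loss and do not describe the sponsor's own calculation.

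A reader might go further and infer that even 70 children are too few for the wristband measures, which are listed among the primary outcome measures, since 13.3% of 70 is 9.3 children and the allowance is 4. The article does not support this. The pilot recorded discomfort. It did not report refusal, removal of the band or missing recordings. Two of 15 is too imprecise to contradict 5.7%. The sizing is tied to change in anxiety, and the participant-involvement section refers to the reported anxiety scale, which all 15 pilot children found acceptable to complete. Some wristband data may be missing, but the article gives no rate for this. It offers no basis for making those outcomes secondary or for writing a lower power for them into the plan.

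**Conclusion.** The two sections disagree: 66 randomised in one, and 70 recruited to secure 66 after dropout in the other. If assignment stops at 33 per group, there is no allowance for losses after randomisation, which is when most of them will occur. At the loss that the protocol itself implies (4/70, about 5.7%), the trial would end with about 31 per group and about 77% power instead of 80%. This assumes a two-sided t-test at 0.05, an effect of d = 0.70 solved backwards from 33 per group, and losses spread evenly over the groups. The contradiction itself depends on none of these assumptions. The effect is modest, but the correction is simple and protects the stated power. The conclusion does not extend to a shortfall in wristband data.

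**What to change.** 1. In *Study flow and layout*, replace the figure with: 35 per group (70 randomised), to give 33 evaluable per group.
2. Prepare the envelope series for 70.
3. In *Calculation of the study's sample size*, state that the allowance is 4/70, about 5.7%, and that it covers losses after randomisation.
4. State that children who do not tolerate the wristband stay in the analyses of the anxiety scale (MCDASf), the Frankl rating and treatment completion.

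The cost is a few words and an envelope list of the right length. No children are added beyond the 70 already planned. If the site has been working to 66, it means four more, two per group. The outcome hierarchy and the stated 80% power do not change.

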**Fig. 1 Fig1:**
[figure not shown]
Flowchart of the study design.

A 1:1 allocation-based block randomisation method will be employed. The method of allocation concealment will be attained by using matching, sealed, serially numbered, non-transparent envelopes that will contain group allocation. The envelopes will be opened in sequence by a non-investigator (dental assistant), only after the envelope has been conclusively dispensed to each partaker and will continue to be anonymous to the clinical team.

At the initial screening visit, the anxiety level will be recorded using MCDASf (Fig. 2) to determine the need for N_2_O sedation and subsequently invite the child and parents to participate in the study. Once enroled, an acclimatising visit will be carried out by a single paediatric dentist who will not be involved in the subsequent treatment of the patients. To be constant, an information script will be organised and rehearsed so that the same preoperative instructions about N_2_O sedation will be delivered to all the children and their parents. The patient’s physiological signs will be recorded using the E4^®^ wrist band (Fig. 3). For the study group only, 15 min of N_2_O sedation will be administered without any dental treatment procedures at the acclimatisation visit.

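### With ages 5–15 and 33 children per arm, the stated unadjusted t-test or Mann–Whitney comparison leaves age variation in the error term; a prespecified age term would recover precision

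*Protocol article*

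**What the plan says.** The relevant statements are all in the protocol article.

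- **Population** (Inclusion and exclusion criteria): "Children (aged 5–15 years old) presenting with their parents" are eligible.
- **Allocation** (Study flow and layout, text after Fig. 1): "A 1:1 allocation-based block randomisation method will be employed". Sealed, numbered envelopes are opened in order. No stratification factor is named, and none is ruled out.
- **Size** (Study flow and layout; Calculation of the study's sample size): 33 per group, and "to compensate for dropouts a total of 70 participants will be recruited for both groups". On power: "The study is sized to have an 80% power to detect a statistically significant difference". No effect size or SD is given.
- **Outcomes** (Primary outcome): change in behaviour and anxiety, measured by E4 parameters including heart rate, by MCDASf before the acclimatisation session and after treatment, and by the Frankl score. Study flow and layout describes the Frankl score only during treatment at the second visit.
- **Analysis** (The study's statistical analysis): two-group differences are tested by t-test or Mann–Whitney, chosen by a normality check, and "A *p*-value of <0.05 will be considered significant in all tests". No age or baseline term is mentioned.

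**The concern.** Five-year-olds and fifteen-year-olds can reasonably be expected to differ in cooperation in the chair, in how they complete a faces scale, and in heart rate. The documents do not quantify this. If age does predict an outcome, a test without an age term treats that predictable variation as noise. In a small trial this has two consequences. Power is lower than the same children could provide. And if the randomisation that occurs leaves one arm noticeably younger, the unadjusted difference mixes the age difference with the effect of the acclimatisation visit, with nothing in the stated analysis to separate them.

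Age is known before allocation, so it is a legitimate covariate that costs nothing to collect.

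**Working it through.** **1. The plan's own figure.** The 33 per group cannot be reproduced, because no effect size or SD is stated. Solving backwards, with two-sided alpha 0.05 (sidedness is not stated) and 80% power:

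d = (1.960 + 0.842) × √(2/33) = 2.802 × 0.246 = 0.69 SD

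(0.70 with the t distribution; 0.61 if one-sided). The allowance from 66 to 70 implies 1 − 66/70 = 5.7% dropout. The value d = 0.69 is used below as the difference that the trial is implicitly sized for.

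**2. How often the arms differ in age.** The age SD is not in the documents. An even spread over 5–15 gives 2.89 (continuous) or 3.16 (whole years); a more concentrated intake gives less. The standard error of the difference in mean age is SD × √(2/33).

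| Assumed age SD (years) | SE of difference (years) | P(difference > 1 year) | P(difference > 1.5 years) |
|---|---|---|---|
| 2.0 | 0.49 | 4% | 0.2% |
| 2.5 | 0.62 | 10% | 1.5% |
| 2.89 | 0.71 | 16% | 3.5% |
| 3.16 | 0.78 | 20% | 5.4% |

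**3. What an imbalance does to the estimate.** With SD 2.89, the 95% limit is 1.96 × 0.71 = 1.39 years. For an age–outcome correlation r (assumed, linear), that imbalance shifts the difference by r × 1.39/2.89 SD: 0.14, 0.24 or 0.34 SD at r = 0.3, 0.5 or 0.7.

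**4. Error rate and power.** These come from 40,000 simulated trials of 33 per arm for each r, with a continuous outcome and age uniform on 5–15. Type I error is under no effect; power is at d = 0.69.

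| r | Type I, t-test, all trials | Type I, t-test, imbalance > 1 year | Type I, ANCOVA on age, imbalance > 1 year | Power, t-test | Power, ANCOVA on age |
|---|---|---|---|---|---|
| 0 | 4.9% | 4.9% | 5.1% | 79% | 78% |
| 0.3 | 5.0% | 7.7% | 5.0% | 79% | 82% |
| 0.5 | 5.0% | 12.2% | 5.1% | 79% | 89% |
| 0.7 | 4.8% | 19.1% | 4.8% | 79% | 97% |

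A hand check agrees. Adjustment shrinks the residual SD by √(1 − r²), so the effective difference is 0.69/√0.91 = 0.72, 0.69/√0.75 = 0.80 and 0.69/√0.51 = 0.97. The normal approximation then gives power of about 84%, 90% and 98%, slightly above the simulated values, as expected.

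**5. Stratifying without adjusting.** Splitting the blocks at age 10 cuts the SD of the age difference from 0.71 to 0.35 years and P(> 1 year) from 16% to 0.5%. If the plain t-test is kept, its type I error falls to 4.1%, 3.0% and 1.3% at r = 0.3, 0.5 and 0.7, and power reaches only 80–83%. The gain comes from the age term, not from the stratification.

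**The case against.** A reader might infer three stronger things, none of which the documents support.

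- *That the comparison is biased or its error rate inflated.* It is not. Randomisation makes chance imbalance part of what the 5% level already covers, and the simulated overall rate is 4.8–5.0% at every correlation. The raised rates apply only to trials in which a large imbalance has occurred.
- *That allocation is unstratified.* The article names no stratum, and one envelope sequence is the natural reading. But blocks can be generated within strata, and a condensed article may leave that to the full protocol. Silence here is not evidence of an error.
- *That stratification is the missing remedy.* Step 5 shows that on its own it gains little.

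Two further objections carry weight. Covariates are often named in an analysis plan, which may exist; but this article does state the between-group test, and neither option it gives can take a covariate, so the stated choice is open to comment. Second, within-child baselines may already absorb part of an age effect: MCDASf is taken before the acclimatisation session, and the E4 band is also worn at the first visit. That weakens the point for anxiety and heart rate. It does not help the Frankl score, which has no described baseline.

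It is also fair that nothing in the documents shows how strongly age predicts these outcomes. If it does not, there is nothing to gain.

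**Conclusion.** The point stands as a modest one about efficiency and robustness. As stated, the analysis leaves age variation in the error term across a 10-year range with 33 per arm. Against an unadjusted power of about 79% at 0.69 SD, an age term is worth roughly 3, 10 or 18 percentage points at correlations of 0.3, 0.5 or 0.7, and costs about 1 point at zero. It also holds the error rate near 5% in those trials, 4–20% of randomisations, where mean ages differ by more than 1 year.

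These figures rest on an assumed age SD, assumed correlations, a linear age effect and a continuous outcome. They show the size to expect for MCDASf and the E4 measures before any baseline adjustment. For the four-level Frankl score they are only a guide. Mann–Whitney was not simulated.

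**What to change.** In The study's statistical analysis, replace the unadjusted two-group comparison with a prespecified model containing arm and age in years:

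- **MCDASf and E4 parameters:** ANCOVA with arm, age and the baseline value. For E4, use as baseline only a first-visit reading taken before any gas is given. The lead-in reading before treatment comes after the acclimatisation visit, so adjusting for it could remove part of the effect.
- **Frankl score:** an ordinal model with arm and age, stating in advance how sparsely filled categories will be handled.

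The cost is one model term for age, plus one for baseline where available. No new data are needed, since age and baseline MCDASf are already known.

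Optionally, stratify the blocks by two age bands, for example 5–9 and 10–15, with one envelope series per band, but only if age is also in the analysis. The cost is a second envelope series and possibly an incomplete block in each band, a group-size difference of one or two children. If strata already exist in the full protocol, name them and include them in the model.
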